##### Main secondary outcomes

Self-efficacy at the second follow-up will serve as a secondary outcome. Self-efficacy is chosen as a secondary outcome due to its predictive value of successful RTW [38–40]. Information on self-efficacy will be collected by standardised paper-and-pencil or online questionnaires during baseline and during follow-ups.

To measure self-efficacy regarding RTW, a German version of the validated return-to-work self-efficacy scale (RTW-SE [41]) will be used. The RTW-SE scale consists of eleven items with a six-point rating scale from 1 = “totally disagree” to 6 = “totally agree”. Example items are “I will be able to cope with setbacks” and “I will be able to concentrate on my work”.

Occupational self-efficacy will be measured by the German version of the validated short form of the Occupational Self-Efficacy Scale [42]. The Occupational Self-Efficacy scale consists of six items with a six-point rating scale from 1 = “not at all true” to 6 = “completely true”. Example items are “I can remain calm when facing difficulties in my job because I can rely on my abilities” and “Whatever comes my way in my job, I can usually handle it”.

Both scales were shown to be reliable by previous research with good to excellent internal consistencies [41, 42]. Therefore, mean scores will be calculated for both scales.

##### Health economic evaluation

Health economic evaluation will be conducted by means of an incremental cost-utility analysis (ICUA) following the net benefit approach [43, 44] from societal perspective [45]. Incremental cost utility ratios (ICUR) will be estimated for estimating the maximum willingness to pay (MWTP) needed for the gain of one quality adjusted life year (QALY) by providing the intervention in comparison to CAU [43, 44]. Comprehensive assessment of health service use and costs will be performed by means of the German version of the client sociodemographic and service receipt inventory (CSSRI [46, 47]) adjusted for CMDs. QALYs will be estimated by means of the EuroQol (EQ-5D-5L [48]) using the German value set [49, 50].

#### Additional data

Additional data will be collected either by standardised interviews conducted by the study psychotherapists or by standardised paper-and-pencil or online questionnaires. For most variables previously published scales will be used. An overview of additional study variables and relevant references is given in Table 1. Scales not being previously published (i.e. days of sickness absence and sociodemographic variables) are provided as supplemental material.

**Table 1 Tab1:** Overview on additional study variables

Variable	Participants	Method
*Interview data*		
Global Assessment of Functioning	All	Global Assessment of Functioning Scale (GAF [30, 31])
Diagnosis	All	Derived from International Neuropsychiatric Interviews (MINI [32])
Indication of treatment	All	
Childhood trauma	All	Childhood trauma screener [51]
Work-related diagnostics	Intervention group	E.g. work history, job description, work tasks, work relationships, person-job fit [25, 33]
*Questionnaire data*		
Sociodemographic variables I	All	Age, gender, work experience
Sociodemographic variables II	All	Marital status, profession, weekly working hours, shift work, leadership position, company size, professional perspective, physical illness
Migration status	All	Basic set of indicators for mapping migrant status; German nationality, parental German nationality [52]
Demands of immigration	Participants with migrant background	Demands of Immigration Scale (DIS [53]
Mental health - depression	All	Depression items of the Patient-Health Questionnaire (PHQ-9 [54–56])
Mental health - anxiety	All	Generalized Anxiety Disorders (GAD-2 [57])
Mental health – somatoform disorders	All	Somatic Symptom Scale 8 (SSS-8 [58])
General health status	All	General health status item of the Veterans RAND 12 (VR-12 [59])
Cultural adaptation	Participants with migrant background	Frankfurt acculturation scale (FRAKK [60, 61])
Work productivity and activity impairment	All	Work productivity and activity impairment Questionnaire (WPAI [62])
Subjective work ability	All	First item of the Work ability index (WAI [63, 64])
Work role functioning	All	Work Role Functioning Questionnaire (WRPQ 2.0 [65]) – short version
Psychosocial working conditions	All	Third version of the Copenhagen Psychosocial Questionnaire (COPSOQ [66, 67]) including scales of job demands, control, development opportunities and social support
Psychosocial safety climate	All	Short version of the Psychosocial Safety Climate Questionnaire [68]
Personality Functioning	All	German version of the Level of Personality Functioning-screener brief form (LPFS-BF 2.0 [69, 70])
Integrated care	All	Modified version of a questionnaire on experiences on integrated care including scales of general coordination and coordination within and between care teams [71]

#### Participant timeline

The schedule of the study including enrolment, intervention and data assessment is given in Table 2.

**Table 2 Tab2:**
[figure not shown]
Schedule of the study

^1^ Work-related diagnostics will be performed during module 1-B

### Diversity issues

In order to meet the ethnic diversity of the insured, the migration background will be documented and analysed as a sociodemographic variable. In addition, the degree of cultural adjustment and post-migratory stress will be assessed with specialized questionnaires [53, 60, 61]. Since studies have shown that migrants benefit less from psychotherapy than natives [72], training (and supervision if needed) regarding culturally sensitive methods will be provided to optimize outcomes for subjects with a migrant background.

### Assignment of interventions

#### Allocation

Eligible participants will be allocated concealed by randomisation using a centralized web based tool (www.randomizer.at) after Module 1-A. Stratification by centre, days of sickness absence within the last 6 months (< 21 days vs. ≥ 21 days) and level of depression measured by the Patient Health Questionnaire-9 (PHQ-9 [54, 55]; ≤ 10 vs. > 10) using block randomisation of variable sizes will be performed.

#### Blinding

Participants will be blinded regarding study hypotheses but it will not be possible to blind them or study psychotherapists to allocation for obvious reasons. Furthermore, all variables at baseline will be collected prior to allocation to minimise reporting and selection bias.

### Data management and analysis

#### Data management

An electronic case report form (eCRF) will be used for data collection. Data from self-reported questionnaires will be collected web-based electronically or paper-based. Paper-based data will be entered into the eCRF by a study assistant. Paper-and-pencil questionnaires will be stored in locked filing cabinets and electronic data will be stored on secured servers. To assure a safe and secure environment for data acquired, data transmission is encrypted with secure socket layer (SSL) technology. Only authorized users are able to enter or edit data and access is restricted to data of the patients in the respective centre. All changes to data are logged with a computerized timestamp in an audit trail. To guarantee high data quality, data validation rules will be defined in a data validation plan. Completeness, validity and plausibility of data will be checked in time of data entry (edit-checks) and using validating programs, which will generate queries. The investigator or the designated representatives are obliged to clarify or explain the queries.

If no further corrections are to be made in the database, eCRF data will be locked. Data will finally be downloaded and used for statistical analysis. All data management procedures will be conducted according to written defined standard operating procedures that guarantee an efficient conduct complying with good clinical practice.

Except contact details of participants, all data will be pseudonymised. Contact details will be stored locally in the study centre in a separate document and are only accessible for authorised staff of the local study centre.

#### Sample size calculations

Sample size calculations were performed with PASS Version 16.0.3. Congruent with results of a recent uncontrolled trial, we expect that participation in psychotherapeutic consultation at work may reduce days of sickness absence from 36 days/6 months to 26 days/6 months at follow-up with a standard deviation of 35 days/6 months for both time points [73]. For the control group, we expect that days of sickness absence will increase from 36 days/6 months to 42 days/6 months due to the lack of work-related treatment in CAU [74] and possibly deterioration of health. The same standard deviation of 35 days/6 months will be expected for the control group. A negative binominal distribution of days of sickness absence will be expected in accordance with previous research [73]. Following those expectations, a dispersion parameter of 2.12 was calculated. To detect this difference with a power of 80% and assuming a two-tailed level of significance of 5%, a sample size of 310 participants with 155 participants for each group is required. Assuming dropout rates of 40% [15], 520 participants shall be recruited for the study in equal proportions per study centre.

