#### Statistical methods

The treatment effect on the primary outcome (days of sickness absence within the last 6 months at the second follow-up) will be analysed using a mixed negative binomial regression model. Treatment group, days of sickness absence within the last 6 months before baseline, gender, age, subjective work ability at baseline as well as the centre will be included as covariates and the respective company as random effect. The primary analysis will be conducted based on the full analysis set according to the intention-to-treat (ITT) principle (i.e. all patients will be analysed in the group they were randomised to).

Missing data for the primary and secondary outcome analysis is assumed to be “missing at random” and replaced using multiple imputation based on predictive mean matching using the covariates of the primary and secondary outcome analysis as potential predictors [75].

As a sensitivity analysis, an evaluation based on the per-protocol (PP) population will be performed. The PP set consists of all participants without major protocol violations. For this analysis, no imputation of missing data will be performed.

In case of significance of the ITT analysis of the primary outcome (two-sided confidence level of 5%), a hierarchical linear mixed model will be used to analyse treatment effects on self-efficacy. This model will include treatment group, self-efficacy at baseline, gender, age, subjective work ability at baseline as well as the centre as covariates and company as random effect. Applying this hierarchical testing strategy, the overall type I error rate will still be controlled.

If no significance of the ITT analysis is achieved, the results of this analysis will be interpreted only in a descriptive sense.

Furthermore, subgroup analyses will be performed to evaluate the role of additional variables (e.g. indication of treatment, type of treatment, symptom severity) on treatment effects on the primary and secondary outcome.

Further collected data (see Table 1) will be analysed using appropriate descriptive methods.

Details of the statistical analysis will be further determined in a statistical analysis plan which will be written before database closure.

All those analyses will be conducted using SAS 9.4 or higher.

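### The dispersion of 2.12 in the sample size calculation contradicts the stated SD of 35 days; the 80% power at 155 per group holds for 2.12, not for the SD

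*Protocol article*

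**What the plan says.** All the planning figures are in the protocol article under Sample size calculations. In the intervention group the consultation "may reduce days of sickness absence from 36 days/6 months to 26 days/6 months at follow-up". The spread attached to these two means is given in the same sentence: "with a standard deviation of 35 days/6 months for both time points". In the control group, "days of sickness absence will increase from 36 days/6 months to 42 days/6 months". For the spread in that group, "The same standard deviation of 35 days/6 months will be expected for the control group". On the distribution: "A negative binominal distribution of days of sickness absence will be expected in accordance with previous research".

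The text then continues: "Following those expectations, a dispersion parameter of 2.12 was calculated". For 80% power at a two-sided 5% level it concludes that "a sample size of 310 participants with 155 participants for each group is required", and it raises the total to 520 for 40% dropout. The software is named (PASS 16.0.3). The test procedure and the derivation of 2.12 are not given.

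Under Statistical methods, the primary outcome "will be analysed using a mixed negative binomial regression model".

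**The concern.** The wording presents 2.12 as a consequence of the means and the SD printed just before it. Under a negative binomial distribution, the mean and the SD together fix the dispersion, so the claim can be checked directly, and it fails at every stated mean.

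The dispersion largely determines the required sample size here, because at means of 26 to 42 days the Poisson part of the variance is negligible. Two incompatible descriptions of the spread therefore lead to two quite different statements of what the trial can detect. That matters most when a result near or below the detection limit has to be interpreted: the reader needs to know whether the trial was planned to find a rate ratio of about 0.63 or could find a weaker effect of about 0.70.

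**Working it through.** **Inputs**, all from Sample size calculations: follow-up means 26 and 42, baseline mean 36, SD 35 in both groups, dispersion k = 2.12, two-sided 5%, 80% power, 155 per group. The normal quantiles are 1.960 and 0.842; their sum is 2.802, and its square is 7.849. The negative binomial variance is V(m) = m + k·m².

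**1. The plan's own figure: does 155 follow from 2.12?** Take a test of the difference in means (42 − 26 = 16), with the null variance evaluated at the average mean of 34:

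- V(26) = 26 + 2.12 × 676 = 1459.12
- V(42) = 42 + 2.12 × 1764 = 3781.68
- V(34) = 34 + 2.12 × 1156 = 2484.72
- n = [1.960 × √(2 × 2484.72) + 0.842 × √(1459.12 + 3781.68)]² / 16² = 154.84, so 155 per group

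Power at 155 is 80.04%. The figure is reproduced exactly. For dropout, 310/0.6 = 517, which fits a target of 520 split equally over five centres (104 each).

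On the log-rate-ratio scale, n = 7.849 × (1/26 + 1/42 + 2k)/ln(26/42)². With k = 2.12 this is 7.849 × 4.302/0.230 = 146.8, so 147 per group, and 155 gives 82% power.

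**2. Does 2.12 follow from SD 35?** k = (35² − m)/m²; conversely, SD = √(m + 2.12·m²).

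| Mean m | k from SD 35 | 1/k | SD implied by k = 2.12 |
|---|---|---|---|
| 26 | (1225 − 26)/676 = 1.77 | 0.56 | 38.2 |
| 36 | (1225 − 36)/1296 = 0.92 | 1.09 | 52.8 |
| 42 | (1225 − 42)/1764 = 0.67 | 1.49 | 61.5 |

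At the average follow-up mean of 34, k is 1.03 and 1/k is 0.97. No entry is 2.12, either as a dispersion or as its reciprocal. With SD 35, a dispersion of 2.12 needs a mean of 23.8 days, which the protocol does not state.

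**3. What SD 35 gives.** On the log-ratio scale with SD 35 in both arms, the variance term is (35/42)² + (35/26)² = 0.694 + 1.812 = 2.507.

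- n = 7.849 × 2.507/0.230 = 85.5, so 86 per group.
- At 155 per group the standard error is √(2.507/155) = 0.127. Then 0.480/0.127 − 1.960 = 1.81, which is about 96% power.
- With a common k of 1.77, the largest value that SD 35 gives at any stated mean, n = 124 and power at 155 is 88%.
- On the difference scale, n = 2 × 1225 × 7.849/256 = 75.1, so 76 per group, and power at 155 is 98%.

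**4. Rate ratio detectable with 80% power at 155 per group**, with the standard error held at its value for 26 versus 42:

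- k = 2.12: exp(−2.802 × √(4.302/155)) = exp(−0.467) = 0.63
- SD 35: exp(−2.802 × 0.127) = exp(−0.356) = 0.70

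**The case against.** The strongest defence is that the sample size is right for the dispersion used. That stands. A reader who tries only the log-rate-ratio formula gets 147 and might infer that 155 is a second error. It is not: a standard difference-in-means calculation returns 155 exactly, and the protocol does not name its procedure, so one formula that misses proves nothing. It is also fair to say that 80% is what the stated means and the stated dispersion give.

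The second defence is that 2.12 may have been taken from the earlier uncontrolled trial that the section cites. That is possible, but the protocol says the value was calculated from the listed expectations, and it does not show how. Arithmetically, 2 × (35/34)² = 2.12, but nothing in the text shows that this was the route.

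Three stronger readings are tempting and not supported:

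- **The trial is underpowered.** For 26 versus 42 days it is not, under either input.
- **An SD of 61 days is impossible for a count of working days in six months.** This needs a maximum number of days, which the protocol does not give.
- **The wrong dispersion will distort the primary analysis.** The planned regression estimates the dispersion from the trial data. The planning value does not enter it, and the choice of standard error can be left to the statistical analysis plan.

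**Conclusion.** The point holds as an internal contradiction. The stated SD and the stated dispersion cannot both describe a negative binomial variable at any of the three stated means. The stated 80% belongs to the dispersion of 2.12 (80% on the difference scale, 82% on the log-ratio scale). Under SD 35 in both arms, power on the log-ratio scale is about 96%, or 88% with a common dispersion of 1.77.

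These figures assume 155 analysed participants per group, follow-up means of 26 and 42, and no allowance for covariates or the company random effect. The log-ratio scale is used on the assumption that the planned model has the usual log link. Whether controls will in fact rise to 42 days is a separate question.

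Because power for the planned comparison is at least 80% either way, this calls for a correction to the sample size justification. It does not threaten the design.

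**What to change.** Correct whichever of the two figures is wrong, the SD of 35 or the dispersion of 2.12. State where 2.12 comes from, which PASS procedure was used and on which scale it tests. Then restate, from that one set of inputs, the power and the detectable rate ratio for 155 completers per group: about 0.63 if 2.12 is kept, about 0.70 if SD 35 is kept.

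The cost is a few sentences in the sample size section. The target of 520, the recruitment plan and the primary model do not change.

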#### Statistical methods

The treatment effect on the primary outcome (days of sickness absence within the last 6 months at the second follow-up) will be analysed using a mixed negative binomial regression model. Treatment group, days of sickness absence within the last 6 months before baseline, gender, age, subjective work ability at baseline as well as the centre will be included as covariates and the respective company as random effect. The primary analysis will be conducted based on the full analysis set according to the intention-to-treat (ITT) principle (i.e. all patients will be analysed in the group they were randomised to).

Missing data for the primary and secondary outcome analysis is assumed to be “missing at random” and replaced using multiple imputation based on predictive mean matching using the covariates of the primary and secondary outcome analysis as potential predictors [75].

As a sensitivity analysis, an evaluation based on the per-protocol (PP) population will be performed. The PP set consists of all participants without major protocol violations. For this analysis, no imputation of missing data will be performed.

In case of significance of the ITT analysis of the primary outcome (two-sided confidence level of 5%), a hierarchical linear mixed model will be used to analyse treatment effects on self-efficacy. This model will include treatment group, self-efficacy at baseline, gender, age, subjective work ability at baseline as well as the centre as covariates and company as random effect. Applying this hierarchical testing strategy, the overall type I error rate will still be controlled.

If no significance of the ITT analysis is achieved, the results of this analysis will be interpreted only in a descriptive sense.

Furthermore, subgroup analyses will be performed to evaluate the role of additional variables (e.g. indication of treatment, type of treatment, symptom severity) on treatment effects on the primary and secondary outcome.

Further collected data (see Table 1) will be analysed using appropriate descriptive methods.

Details of the statistical analysis will be further determined in a statistical analysis plan which will be written before database closure.

All those analyses will be conducted using SAS 9.4 or higher.

For the health economic evaluation, stochastic uncertainty of ICUR will be estimated by means of non-parametric bootstrapping with 2000 replications [76]. ICUR will be interpreted based on the cost-effectiveness plan [43]. MWTP necessary for the gain of one QALY by the implementation of the intervention in comparison to CAU will be estimated for the threshold range between 0 and 125.000€ [77] based on the cost effectiveness acceptability curve [43, 44, 76]. The health economic evaluation will be conducted using STATA 16.

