#### Intervention

All sessions of psychotherapeutic consultation at work will be conducted by licenced psychological or medical psychotherapists or by psychological or medical psychotherapists being in an advanced state of postgraduate training for psychotherapy. The intervention consists of three modules. The first module includes one session of basic diagnostic assessment on mental health (Module 1-A) and one session of work-related diagnostic assessment (Module 1-B). Whereas Module 1-A will be offered to the intervention and control group, Module 1-B and all other modules will exclusively be offered to the intervention group. Based on mental health assessment, participants of the control group will receive recommendations for treatment in CAU (e.g. in- or outpatient acute care, inpatient vocational rehabilitation). Participants of the intervention group will be transferred to CAU if outpatient work-related treatment would not sufficiently cover the individual need for treatment or will receive Module 2. In case participants of the intervention group are transferred to CAU, potential waiting times for treatment will be bridged by Module 2. Module 2 will include up to ten sessions of work-related psychotherapeutic consultation or treatment. Participants of the intervention group with an inability to work will receive further psychotherapeutic consultation during their RTW process in up to five sessions during Module 3. Participants of the intervention group may thus receive up to 17 sessions of psychotherapeutic consultation (Module 1-A: one session; Module 1-B: one session; Module 2: ten sessions; Module 3: five sessions). For both, the control and intervention group, a medical report will be prepared. Participants of the intervention group who received up to four sessions of psychotherapeutic consultation and participants of the control group will receive a follow-up call by study therapists twelve weeks after their last visit. In this call, participants will be asked on how they have coped so far and whether further help regarding treatment in CAU is needed. For all other participants, an equal follow-up will be performed during their last session of psychotherapeutic consultation.

A schematic overview of the intervention is given in Fig. 1 and all its components are further described below.

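### If outcomes vary by therapist in the intervention arm, the planned models, with company as their only random effect, understate the standard error of the treatment effect

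*Protocol article*

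**What the plan says.** Randomisation is of individual participants, 1:1, stratified by centre, prior sickness absence and PHQ-9 level (Allocation). Company is not a stratification factor.

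On delivery, the Intervention section states: "All sessions of psychotherapeutic consultation at work will be conducted by licenced psychological or medical psychotherapists", or by such psychotherapists in an advanced stage of postgraduate training. Module 1-A is given to both arms, while "Module 1-B and all other modules will exclusively be offered to the intervention group". The session limits are 1 for Module 1-B, 10 for Module 2 and 5 for Module 3, so up to 16 sessions are given in one arm only.

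Under Statistical methods, the primary model contains treatment, baseline sickness absence, gender, age, baseline work ability and centre as covariates, and "the respective company as random effect". The self-efficacy model, tested only if the primary analysis is significant, again has company as its single random effect. The sample size calculation contains no allowance for clustering.

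**The concern.** Patients treated by the same therapist may have correlated outcomes. Here that correlation would arise mainly in the intervention arm, because only that arm receives the course of sessions. This is a partially nested design. A model that ignores the nesting treats the intervention patients as independent (given company and centre) and so credits the intervention mean with too much precision.

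The company intercept does not cure this. It is common to both arms, and companies can contribute patients to both, so it largely cancels from the treatment contrast. Therapist variation present in one arm only does not cancel.

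At stake are the width of the primary confidence interval and the primary p-value, which also decides whether self-efficacy is tested confirmatorily. The article says that a later statistical analysis plan will add detail, but it already fixes the random-effects structure of both models. The point therefore concerns a stated choice, not a missing detail.

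**Working it through.** **Inputs from Sample size calculations.** Follow-up means of 26 days (intervention) and 42 days (control), dispersion 2.12, two-sided 5%, power 80%, 155 per arm, dropout 40%, 520 recruited.

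**Inputs assumed.** Number of therapists J = 10 to 30 and therapist ICC = 0 to 0.05. The documents give neither.

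**1. The plan's own figure.** The negative binomial formula gives

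n per arm = (1.96 + 0.842)² × (1/42 + 1/26 + 2 × 2.12) / [ln(26/42)]² = 7.85 × 4.302 / 0.230 ≈ 147.

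The stated 155 is about 5% higher and has 82.1% power under this formula, so it is not reproduced exactly. The dropout step is: 310/0.6 = 517, rounded to 520. Nothing in the derivation refers to therapist. The difference between 147 and 155 does not affect the present point.

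**2. Closed form for one-arm clustering.** With m = 155/J patients per therapist:

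- design effect in the intervention arm: DE = 1 + (m − 1) × ICC
- true variance / model variance of the contrast: (1 + DE)/2, taking the arms as equally variable
- actual type I error: 2 × [1 − Φ(1.96 / √((1 + DE)/2))]

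Example, J = 10 and ICC = 0.05: m = 15.5; DE = 1 + 14.5 × 0.05 = 1.725; (1 + 1.725)/2 = 1.3625; square root 1.167; 1.96/1.167 = 1.679; type I error 9.3%.

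| Therapists | m | ICC | DE | True SE / model SE | Type I error |
|---|---|---|---|---|---|
| any | – | 0 | 1 | 1.00 | 5.0% |
| 30 | 5.2 | 0.01 | 1.042 | 1.01 | 5.2% |
| 10 | 15.5 | 0.01 | 1.145 | 1.04 | 5.8% |
| 20 | 7.8 | 0.05 | 1.337 | 1.08 | 7.0% |
| 15 | 10.3 | 0.05 | 1.467 | 1.11 | 7.8% |
| 10 | 15.5 | 0.05 | 1.725 | 1.17 | 9.3% |

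**3. Does the company intercept absorb it?** This was checked by simulating a normal-outcome analogue with centre fixed and a company random intercept (155 per arm, 15 therapists, 6,000 runs per setting; assumed 8 companies per centre and company ICC 0.02). The true average effect was zero.

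- ICC 0: 4.9% rejections
- ICC 0.02: 7.0%
- ICC 0.05: 8.3%, and 8.6% when each company is served by a single therapist

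At ICC 0.05 the mean model standard error was 0.1127 against an actual standard deviation of the estimate of 0.1268, a ratio of 1.13. The closed form gives 1.11. The excess is absent at ICC 0 and remains with the company term in the model.

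**The case against.** **The inflation is conditional.** A reader might infer that the type I error of this trial does exceed 5%. The documents do not support that, because they give no ICC, therapist number or caseload. If the sessions affected nobody, they would create no therapist variance and the test would keep its 5%. The inflation concerns a zero average effect with therapists differing around it. This stands, and the point is worded accordingly.

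**An ICC of 0.05 may be large for this outcome.** On the log scale, with dispersion 2.12, the residual variance is about 2.12 + 1/26 = 2.16. ICC 0.05 then implies a therapist variance of 2.16 × 0.05/0.95 = 0.114, a standard deviation of 0.34. The 95% range of therapists would run from about 0.52 to 1.94 times the average number of sickness days. That is wide beside the planned ratio of 26/42 = 0.62, for an outcome read at fifteen months. At ICC 0.01 the standard deviation is 0.15 and the inflation is slight. This stands as a reason to read the lower rows of the table as the upper part of the range.

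**Exposure is not cleanly one-armed.** Sixteen sessions is a maximum, treatment may end early or pause, and controls have Module 1-A and a follow-up call from study therapists. This reduces the arm-specific effect but does not remove it.

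**The simulation is not the planned model.** It uses a normal outcome, without the negative binomial likelihood, the baseline covariates or the multiple imputation. It supports the direction and approximate size only.

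**The testing hierarchy is sound.** A reader might also infer that the article's statement on overall type I error control is wrong. It is not: that statement concerns multiplicity, and the fixed order is valid. What remains is that the self-efficacy test depends on a primary p-value that would be too small if therapists differ.

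**Conclusion.** The point holds in conditional form. Both models name company as the only random effect, although up to 16 therapist-delivered sessions occur in one arm. Any positive therapist variance in that arm makes the standard error too small, and neither the centre terms nor the shared company intercept corrects this. The confidence interval would also be too narrow when the treatment works.

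For 10 to 30 therapists, ICC 0.01 to 0.05 and 155 analysed per arm, type I error runs from 5.2% to 9.3% and the standard error is understated by a factor of 1.01 to 1.17. Every figure above 5% rests on assumed values. The defect is modest to moderate and inexpensive to correct.

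**What to change.** 1. Make sure that a pseudonymised code for the treating therapist is held with the session data. Adherence to the study protocol already provides for documenting modules, session numbers and dates. The eCRF field list is not shown, so the code may already be there.
2. Add to the primary and the self-efficacy model a therapist random effect that acts only in the intervention arm (partially nested model), use small-sample degrees of freedom, and report the therapist variance. If that variance is estimated at zero, the model reduces to the planned one.
3. Fix in advance what is done if the negative binomial model does not converge or gives a boundary estimate, which is a real possibility with few therapists. The performance of the extended model has not been simulated here.

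**Cost.** At most one data field, one model term and a somewhat wider interval if therapists differ. The corrected standard error also shows the power that is really available. For 15 therapists at ICC 0.05, 155 per arm would have Φ(2.88/1.11 − 1.96) ≈ 74% instead of 82%, where 2.88 = 0.480/√(4.302/155).
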